## Abstract

**Background:**

Hospital-at-home (HaH) programs provide an effective and safe alternative to conventional hospitalization, particularly for patients with multimorbidity or complex chronic conditions. In this setting, nursing assessment plays a key role, given the intermittent nature of care and the limited presence of other professionals. However, nursing documentation in HaH remains challenging because of organizational heterogeneity, fragmented records, and the coexistence of multiple assessment tools that create redundancy and compromise information quality. The overall objective of this study is to develop and validate a meta-instrument (VALENF-HAD) that integrates the assessment of functional capacity, pressure injury risk, fall risk, frailty, nutritional status, and sleep quality in patients admitted to hospital-at-home units on the basis of the analysis of other validated measurement instruments used in nursing assessment.

**Methods:**

A multicentre, cross-sectional study will be conducted in four public hospitals in Castellón Province, Spain. Participants will include adults (≥18 years) admitted to HaH units. Sociodemographic and care-related variables, along with risk-related variables, will be collected using the following instruments: functional capacity (Barthel Index and Lawton & Brody Scale), risk of pressure injuries (Braden Scale), risk of falls (STRATIFY Scale), frailty (FRAIL questionnaire), nutritional status (Nutritional Screening Initiative tool), and sleep quality (Athens Insomnia Scale). The development process of the meta-instrument consists of four phases: (I) analysis of instruments, constructs, and items; (II) meta-instrument design; (III) initial validation; and (IV) determination of clinimetric properties.

**Discussion:**

This study is expected to produce a parsimonious and specific meta-instrument for hospital-at-home settings that is capable of integrating functional, nutritional, sleep, fall risk, frailty, and pressure injury assessments. Its implementation will enhance the quality and standardization of nursing documentation, reduce administrative workload, facilitate early risk detection, and free up time for direct patient care. Ultimately, this study will contribute to advancing evidence-based nursing practices in home hospitalization.

## Background

Hospital-at-home (HaH) care represents an efficient alternative to conventional inpatient care for numerous medical and surgical conditions [1]. It is defined as a hospital-level care modality delivered in the patient’s home providing active monitoring and treatment for the patients who would otherswise require acute hospital care. Fro conceptual perspective, HaH encompasses two main operational models: admission avoidance (preventing hospitalization) and early discharge (shortening hospital stay), when patients do not require hospital facilities but still need active monitoring [2]. Both are aimed at reducing costs and complications associated with the hospital environment [3,4]. In Spain, HaH was implemented in 1981, although its development has been uneven and limited by the lack of a regulatory framework and the heterogeneity of organisational models [1].

Nursing care at home differs substantially from hospital-based care, as it is intermittent and often delivered in the absence of other health care professionals [5]. These circumstances increase nurses’ responsibility in clinical decision-making and require high-quality assessments to ensure effective interprofessional communication [6]. Moreover, home care constitutes one of the main settings for managing patients with complex chronic multimorbidity, characterised by heterogeneous needs that range from low-intensity care to high-dependency, complex clinical support [7]. Central to this model is a biopsychosocial approach, where social and family dynamics are prioritized alongside clinical stability. This framework fosters shared responsibility, integrating patient autonomy with the essential role of the caregiver network to ensure the safety and continuity of the hospital-level care provided at home [1].

In this context, nursing records are an essential component of medical records, as they document the patient’s status and progress, enable risk identification, and ensure continuity of care despite less frequent visits compared with hospital settings [8,9]. Accurate and complete documentation of nursing assessments helps prevent errors and improves communication among professionals [10]. However, its use in home settings is less consistent than it is in hospitals [11], largely because of structural and organisational differences between both contexts. Home care usually involves longer and more fragmented care episodes, wich may hinder both the standardization of documentation and the systematic assessment of patients’ needs and risks [12]. Furthermore, the coexistence of multiple assessment tools leads to construct overlap and redundancy, compromising the quality and validity of records [13,14]. Evidence suggests that in both hospital [15] and home settings [7,16], simplifying documentation and implementing systematic screening could ensure the collection of essential information.

The available information on integrated and validated instruments for nursing assessment in HaH is limited. Several systematic reviews highlight the lack of consensus on indicators that capture the quality of nursing care [17,18] and the scarcity of tools adapted to complex care settings, wich have been predominantly developed and studied in older populations [19]. In this regard, the Fundamentals of Care Framework [20] provides a relevant reference, particularly in its physical care dimension. This framework identifies essential care needs such as hygiene, mobility, nutrition, prevention of pressure injuries, rest, and elimination, which are interrelated with the therapeutic relationship and the care context [21,22]. Its application in HaH enables a comprehensive, person-centred nursing assessment and facilitates the identification of outcomes that are sensitive to nursing practice, such as functional decline [23], sleep disturbances [24], or malnutrition [25]. Moreover, this framework offers a robust conceptual basis for incorporating dimensions that allow the synergistic identification of risks such as falls [26], pressure injuries [27], and frailty [28].

An innovative proposal to overcome these limitations is the development of meta-instruments, understood as integrated assessment instruments that combine items and constructs from multiple validated tools into a single parsimonious instrument while maintaining clinimetric properties and diagnostic capacity equivalent to those of the original tools [29]. For instance, the VALENF Instrument [30,31] is a predictive algorithm that estimates functional capacity, pressure injury risk, and fall risk by merging the Barthel, Braden, and Downton scales into a seven-item solution. This meta-instrument has shown high predictive accuracy and reliability for the original scales’ total scores, along with adequate clinimetric properties.

Adapting this approach to hospital-at-home care could optimize nurses’ time, enhance the early detection of risks, and promote the standardization of care [16]. Therefore, it seems pertinent to develop and validate a specific meta-instrument for hospital-at-home settings aimed at supporting more parsimonious, standardized, and person-centred nursing practices. This instrument, named VALENF-HAD (from the Spanish VALoración ENFermera–Hospitalización A Domicilio, meaning “Nursing Assessment – Hospital-at-Home”), is designed to integrate multiple dimensions of nursing assessment in hospital-at-home settings, including functional capacity, pressure injury risk, fall risk, frailty, nutritional status, and sleep quality.

The overall objective of this study is to develop and validate a meta-instrument (VALENF-HAD) that integrates the assessment of functional capacity, pressure injury risk, fall risk, frailty, nutritional status, and sleep quality in patients admitted to hospital-at-home units based on the analysis of validated nursing assessment instruments. Specifically, the study aims to identify patient profiles with similar care needs based on nursing assessment, analyse the influence of sociodemographic and care-related variables on assessment outcomes, examine the relationships among the included instruments to identify redundant items, and determine the clinimetric properties of the VALENF-HAD meta-instrument, including content validity, construct validity, and internal consistency.

## Methods

### Design

This multicentre, cross-sectional study involves the consecutive recruitment of patients admitted to the hospital-at-home (HaH) units of four public hospitals in the province of Castellón, Spain. These hospital-at-home units are organizationally integrated within the participating hospitals and provide hospital-level care delivered in patients’ home. At the time of manuscript submission, the study is in the recruitment and data collection phase. The planned study timeline is as follows: a) participant recruitment and data collection form 01/02/2025 to 31/05/2026; b) database download and data curation from 01/06/2026 to 31/08/2026; c) data analysis from 01/09/2026 to 31/08/2027; d) dissemination of study results from 01/09/2027 onward. The overall study timeline is shown in Fig 1.

**Fig 1 pone.0351126.g001:**

Timeline of the study.

### Participants and sample

The study population will consist of nursing assessments performed on adult patients receiving Hospital-at-Home care in four public hospitals in the province of Castellón (Spain), which together provide health care coverage to 615.188 people: Hospital Universitario Comarcal de Vinaròs (HUCV), Hospital Universitario de La Plana (HULP), Consorcio Hospitalario Provincial de Castellón (CHPC), and Hospital General Universitario de Castellón (HGUCS).

The study will include nursing assessments conducted within the first 48 hours after admission for patients aged 18 years or older who agree to participate and provide written informed consent, as the assessment instruments included in the study are primarily validated in adult populations. The first hours were selected because they correspond to the initial nursing assessment period in hospital-at-home units, allowing for a standardized baseline evaluation. Assessments from patients whose expected stay is less than 48 hours, such as those admitted under a day hospital regimen, will be excluded.

Regarding sample size, the literature recommends including between 5 and 10 participants per item in studies aimed at the development and validation of questionnaires [32]. The total number of items across all the instruments considered in this study is 59; therefore, a minimum of 590 assessments was initially estimated. However, due to the lack of specific recommendations for studies involving the integration of multiple assessment instruments and based on previous methodological references [29], the sample size was increased to 1.180 assessments to ensure adequate representativeness and to support more complex analytical strategies.

The sample will be stratified according to the number of admissions in each HaH unit, excluding 20% corresponding to day-hospital admissions. Consecutive sampling will be performed in each until the required sample size is reached, as shown in Table 1.

**Table 1 pone.0351126.t001:** Sample size estimation.

Hospital	Admissions in 2022	Average monthly admissions	Estimated n (12 months)
HUCV	1.136	94	318
HULP	1.105	92	311
CHPC	889	74	251
HGUCS	1.066	88	300
**TOTAL**	4.196	348	**1.180**

### Variables and instruments

Sociodemographic variables are included (age, sex, educational level, marital status, type of cohabitation, presence of a caregiver, type of caregiver, and place where care is provided); variables related to the care process (hospital, source of admission, type of process, clinical profile, advanced or terminal palliative situation, Charlson Comorbidity Index [33], active infection on admission, pressure injury on admission, bedridden status, presence of invasive clinical devices, polypharmacy, pain, and presence of symptoms assessed using the Edmonton Symptom Assessment System [34]; and palliative sedation status, which is measured with the RAMSAY Sedation Scale [35].

Variables related to the nursing assessment will be collected, including functional capacity, measured with the Barthel Index [36] and the Lawton and Brody scale [37]; pressure injury risk, measured with the Braden Index [38]; and fall risk, measured with the STRATIFY scale [39]. These assessments will be recorded in the data collection form together with the VALENF Instrument [30], a meta-instrument that integrates the assessment of functional capacity, pressure injury risk, and fall risk. In addition, frailty will be measured with the FRAIL questionnaire [40], nutritional status with the NSI tool [41], and sleep quality with the Athens Insomnia Scale [42].

### Data collection

Data collection will be conducted prospectively over an estimated 16-month period (01/02/2025 to 31/05/2026) through consecutive sampling in the home hospitalization units participating in the study. The time required for a complete evaluation in routine clinical practice is approximately 20 minutes. Data will be collected within the first 48 hours after admission, allowing for an initial assessment on the first day followed by a more comprehensive evaluation on the second. This phased approach has been designed to reduce the pressure of the first visit and minimize potential fatigue among both patients and clinical staff. Furthermore, the HaH model allows for longer and more flexible interaction with patients compared to conventional hospitalization. Data entry will be carried out using Research Electronic Data Capture (REDCap) software.

A common Standard Operating Procedure (SOP) was developed for all participating centers, detailing the instructions for instrument administration and data recording. Prior to the start of data collection, structured training sessions were conducted at each participating hospital to ensure consistency in the application of the instruments by nursing professionals. During the data collection period, continuous monitoring mechanisms were established to ensure measurement consistency, including regular communication between the research team and clinical staff, as well as periodic data quality checks to identify potential inconsistencies or deviations in data collection.

After informing patients and providing them with the study information sheet, written informed consent will be obtained. Decision-making capacity will be clinically assessed by the nursing team as part of routine care, based on the patients’s ability to understand the study information and provide informed consent. In cases where patients present cognitive impairment or are unable to provide valid consent, informed consent will be obtained from a legally authorized representative (LAR), in accordance with standard ethical procedures.

When necessary, the primary caregiver and/or family member will complete the questionnaires as proxy respondents. Proxy responses will be explicity identified in the dataset, allowing them to be distinguished from patient self-reported data.

Both the nursing professionals and the research team signed a confidentiality and data responsibility agreement, as well as an intellectual property commitment.

### Statistical analysis

The statistical analysis will be conducted in four sequential phases. First, the sample and measurement instruments will be characterized through a descriptive analysis according to the nature of the variables. Significant differences in the assessment results of problems related to hospitalization will be examined, considering sociodemographic and care process variables, taking into account whether the data are patient self-reported or proxy-reported. The normality and homoscedasticity of the sample will be tested using the Kolmogorov–Smirnov and Levene tests, respectively. Depending on the results, Student’s t test or ANOVA will be applied, depending on the number of groups. Categorical variables will be analysed using the chi-square (χ²) test, and correlations will be assessed using Pearson’s or Spearman’s test, as appropriate. When the assumptions for these tests are not met, the corresponding nonparametric tests will be applied.

Following this initial analysis, the development and validation process of the new meta-instrument will be carried out by adapting the methodological proposal of Llagostera-Reverter et al. [29]. First, an analysis will be performed to explore the conceptual and semantic relationships among the dimensions of the instruments. In addition, the items of the instruments will be analysed to identify similarities, duplications, and redundancies, with the goal of establishing direct or indirect conceptual relationships through a nominal group [43] composed of members of the research team and nursing professionals working in home hospitalization units and analysing nursing physical care within the conceptual framework of the Fundamentals of Care [44]. Subsequently, conceptual similarities and redundancies between the dimensions and items of the instruments will be examined, and correlations will be tested using Pearson’s or Spearman’s tests, as appropriate. Multiple correspondence analysis and cluster analysis will be used to explore potential groupings of items and to identify clinical profiles of patients with similar care needs [45–47].

Second, linear model analyses will be performed using each assessment instrument as a dependent variable to determine the influence of sociodemographic and care process variables. Additional linear model analyses will be conducted to predict the scores of the original instruments on the basis of combinations of their own items.

Third, the initial validation of the new meta-instrument will be conducted. Agreement will be assessed using the intraclass correlation coefficient (ICC > 0.7) [48]. Participants will also be grouped according to the categorical levels of each assessment instrument on the basis of their obtained scores, and overall and category-specific agreement will be examined using Kendall’s tau-b and Cohen’s kappa tests (τ-b and κ > 0.7) [49]. To ensure the robustness and generalizability of these predictive models, cross-validation will be applied [50].

Fourth, the clinimetric properties will be determined following the recommendations of the COSMIN initiative [51]. Content validity will be evaluated through a nominal group of clinical nurses with at least 10 years of experience and university nursing faculty with doctoral degrees. They will assess the relevance of the proposed items and dimensions using the Polit and Beck (2006) methodology to calculate the item-level content validity index (I-CVI ≥ 0.78) and the scale-level content validity index (S-CVI ≥ 0.9) [52]. Construct validity will be assessed according to the methodology proposed by Efron and Tibshirani [53]. The sample will be randomly divided into two subgroups. In the first subgroup, an exploratory factor analysis with oblimin rotation and maximum likelihood estimation will be performed after verifying adequacy through Kaiser–Meyer–Olkin and Bartlett’s sphericity tests. In the second subgroup, confirmatory factor analysis and structural equation modelling will be conducted to validate the theoretical structure of the instrument. Model fit will be evaluated using χ²/df (<5), RMSEA (<0.05), and CFI (≥0.97). Internal consistency will be estimated using McDonald’s Omega (Ω > 0.7) [54] and Cronbach’s alpha (α > 0.7), as appropriate, depending on the characteristics of the data and the underlying assumptions of each method [55]. Finally, interrater reliability will be assessed in a pilot sample using the intraclass correlation coefficient (ICC > 0.61). A p value < 0.05 will be considered to indicate statistical significance, and analyses will be conducted using software, selected according to their specific analytical capabilities for descriptive, multivariate, and advanced modelling procedures.

The Statistical Analysis Plan (SAP) was defined during the study design phase, prior to the start of participant recruitment. This plan remained stable throughout the study and was considered finalized before the initiation of data analysis. The study was retrospectively registered (ISRCTN 94528203, 09/05/2025), including the objectives, variables, and analytical strategies. No relevant changes were made after the start of recruitment.

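### ICC > 0.7 between a total and a prediction from its own items is a lenient part-whole criterion that cannot by itself show that the removed items were redundant

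*Protocol article*

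**What the plan says.** In the Statistical analysis section of the protocol article, the second phase announces linear models to "predict the scores of the original instruments on the basis of combinations of their own items". The third phase, the initial validation, then states: "Agreement will be assessed using the intraclass correlation coefficient (ICC > 0.7". It continues with a categorical check, in which "overall and category-specific agreement will be examined using Kendall’s tau-b and Cohen’s kappa tests (τ-b and κ > 0.7", and ends: "To ensure the robustness and generalizability of these predictive models, cross-validation will be applied".

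The article does not name the two quantities that enter the ICC. Given the order of the steps and the reference back to the predictive models, the natural reading is the observed total of each original instrument against the total predicted from a reduced set of its items. Items and total come from the same assessment, since the study uses one set of "nursing assessments conducted within the first 48 hours after admission" per admission.

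The Background describes meta-instruments in general as "maintaining clinimetric properties and diagnostic capacity equivalent to those of the original tools". The article does not say whether the ICC, tau-b and kappa thresholds must all be met.

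**The concern.** A total contains its own items. When a prediction is built from some of them, the kept items enter both sides of the comparison with identical values and identical measurement error. Part of the agreement is then guaranteed by construction and says nothing about the items that were removed. Whether those items carry information that the kept ones lack is what a reduced instrument has to settle.

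If the threshold is low enough to be met largely through this overlap, a pass would be reported as agreement with the original scale. Individual patients could still have predicted scores far from their observed ones.

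**Working it through.** **Inputs.** From the article: ICC > 0.7; prediction of each instrument's score from its own items; tau-b and kappa > 0.7 on categories; 59 items and 1180 planned assessments. Not given: inter-item correlations, item variances, the number of items kept and the SD of each scale. These are assumptions where used below.

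**The plan's own figures.** The threshold 0.7 is a chosen value with no derivation to reproduce. The sample size reproduces: 59 × 10 = 590 and 2 × 590 = 1180. The point does not depend on it.

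**Step 1: what ICC = 0.70 means.** Let T be the observed total and P its least-squares prediction with intercept. Then mean(P) = mean(T) and cov(P,T) = var(P) = R²·var(T). The single-measure ICC (agreement or consistency) is

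ICC = 2·cov(P,T)/(var T + var P) = 2R²/(1 + R²), so R² = ICC/(2 − ICC).

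At ICC = 0.70, R² = 0.70/1.30 = 0.538. Other values:

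| R² | ICC |
|---|---|
| 0.50 | 0.667 |
| 0.60 | 0.750 |
| 0.70 | 0.824 |
| 0.80 | 0.889 |

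If an average-measures ICC were used, 0.70 would correspond to a single-measure value of 0.538, and R² = 0.538/(2 − 0.538) = 0.368.

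**Step 2: individual error at the threshold.** Residual SD = √(1 − 0.538) = 0.68 SD of the scale. The 95% limits of agreement are ±1.96 × 0.68 = ±1.33 SD. On a 0–100 scale with an assumed SD of 20 to 35, this is about ±27 to ±47 points.

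**Step 3: how much is overlap.** For a summed score write T = K + D, with K the sum of the kept items and D the sum of the dropped ones. The prediction from the kept items is P = K + D̂, so T − P = D − D̂. All the error lies in D, while K is reproduced exactly. If m items are uncorrelated with equal variance and k are kept, D̂ is a constant (the kept items tell nothing about the dropped ones), yet R² = k/m. Keeping 60% gives ICC = 2 × 0.6/1.6 = 0.75.

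**Step 4: simulation check.** 1180 patients, independent items scored 0–2, 10-fold cross-validated predictions, 200 replicates. Item counts are illustrative.

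| Kept | R² | ICC | ICC > 0.7 |
|---|---|---|---|
| 6 of 10 | 0.60 | 0.75 | 100% |
| 5 of 8 | 0.62 | 0.77 | 100% |
| 3 of 5 | 0.60 | 0.75 | 100% |
| 5 of 10 | 0.50 | 0.66 | 2.5% |

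The mean correlation between kept-item and dropped-item sums was about 0 throughout. Cross-validation left the ICC essentially at its theoretical value: it corrects overfitting, not shared content.

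**Step 5: the companion criteria.** At a median split under normality, kappa = (2/π)·arcsin(√R²). At R² = 0.538 this is 0.525. For kappa = 0.7, R² = sin²(0.7π/2) = 0.79, which corresponds to ICC = 2 × 0.794/1.794 = 0.885. In the 6-of-10 simulation, with categories cut at the tertiles of the observed total, kappa was 0.41 and tau-b 0.59. No replicate passed all three criteria.

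**The case against.** A reader might infer from the algebra that the meta-instrument would be declared valid with 54% of the variance recovered, or that arbitrary deletion of 40% of the items would pass validation. The documents do not support that.

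- **Companion criteria.** Tau-b and kappa > 0.7 stand in the next sentence and are considerably stricter. The case of 6 unrelated items out of 10 fails them.
- **Item selection and later checks.** Items are to be chosen through conceptual analysis, a nominal group, correlations, and correspondence and cluster analysis. Content validity, factor analysis, and omega or alpha follow. Mutually unrelated items would have alpha near zero and no factor structure. The unrelated-items case is therefore a limiting case, and real items are probably correlated, which raises R² for the same number kept.
- **Equivalence.** The equivalence wording is a general definition in the Background. Nowhere is ICC > 0.7 said to establish equivalence.
- **Overlap is inherent.** The task is to recover the original total from fewer items, so the total is a proper target.
- **Level of detail.** The ICC form and any confidence-bound rule may be in the analysis plan, which is not shown.

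All of this stands, and it limits the consequence. It does not remove the point. The 0.54 pass mark does not depend on the items being unrelated. Tau-b and kappa are computed on the same overlapping quantities and give no error in scale points. If the three criteria are judged separately, the ICC is lenient. If all are required, an ICC threshold of 0.7 adds little beside a kappa threshold that needs an ICC of about 0.885 at a median split.

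A literal reading of the own-items phrase might also suggest that overlap between scales cannot be used at all. The article plainly examines redundancy between instruments, so this is at most a wording matter.

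**Conclusion.** The point holds in limited form: this should be fixed, but it is not a fatal flaw. The only agreement criterion on the continuous score is met by a least-squares prediction once R² exceeds 0.538, with limits of agreement of about ±1.33 SD at that point. Part of what it measures is overlap that cross-validation does not remove. A pass on the ICC alone cannot show that the removed items were redundant or that the reduced score is interchangeable with the original.

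This rests on three things: the inferred pairing of observed and predicted total, a least-squares prediction, and a single-measure ICC (an average-measures form would lower the pass mark to 0.368). The figures in scale points also need the assumed SD and describe the floor of the criterion, not an expected result. The companion kappa figure of R² ≈ 0.79 assumes normality and a median split; the instruments' real cut-offs will give other values.

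**What to change.** 1. Keep the ICC, tau-b and kappa. State that the comparison is observed against predicted total, that all three thresholds must be met for each instrument, and that they are evaluated on cross-validated predictions.
2. For each instrument, add the cross-validated 95% limits of agreement in scale points, judged against an acceptable error fixed before the analysis starts.
3. Report, as the part-whole benchmark, the agreement between the sum of the dropped items and its prediction from the kept ones. Alternatively, show the ICC expected from k of m unrelated items, 2(k/m)/(1 + k/m), beside the observed ICC. This is best reported rather than used as a pass mark: with only one or two items dropped it can be low although the total is well recovered.

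Optional and secondary: apply the ICC threshold to the lower 95% confidence bound, and say explicitly whether items of one instrument may predict the score of another.

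Cost: wording and a few lines of analysis. No new data are needed, because the Data management plans section refers to an item-level dataset. The change can be made before analysis begins on 01/09/2026. The downside is that reported agreement may look less favourable and more items may have to be retained.

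### Score-level agreement rests on one pooled ICC > 0.7, which depends on case mix and can hide large error among patients with care needs

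*Protocol article*

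**What the plan says.** The third analysis phase (Protocol article, Statistical analysis) sets the criterion for the scores themselves: "Agreement will be assessed using the intraclass correlation coefficient (ICC > 0.7"). It names no subgroup and no measure of error in score points.

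A second criterion applies after the scores are categorised. "Participants will also be grouped according to the categorical levels of each assessment instrument on the basis of their obtained scores", and then "overall and category-specific agreement will be examined using Kendall’s tau-b and Cohen’s kappa tests (τ-b and κ > 0.7"). Internal validation is one sentence: "To ensure the robustness and generalizability of these predictive models, cross-validation will be applied".

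The predicted scores come from linear models on combinations of each instrument's own items. The sample is broad. Under Participants and sample, assessments are included "for patients aged 18 years or older who agree to participate and provide written informed consent"; the only stated exclusion is an expected stay under 48 hours. The first phase derives patient profiles with similar care needs, but the agreement analysis does not use them.

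**The concern.** A fixed limit on the ICC is not a fixed limit on error. With the same prediction error, a more varied sample gives a higher ICC. Patients who score at the no-need end of every item add spread, and any subset of items predicts their total easily.

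The Background describes home-care patients as "characterised by heterogeneous needs that range from low-intensity care to high-dependency, complex clinical support". That sentence is about home care in general and does not describe this sample, but the eligibility criteria do nothing to narrow the range.

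The instrument is meant to support early risk detection while keeping the diagnostic capacity of the original tools. That purpose concerns mainly patients who have needs. A pooled ICC above 0.7 could come largely from the contrast between patients with and without needs, and it would not carry over to a unit with a different case mix.

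**Working it through.** **The plan's own figures.** The document gives no expected ICC, tau-b or kappa to reproduce. The sample size does reproduce: 59 items × 10 = 590, and 59 × 20 = 1,180. It has no bearing on this point.

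**Step 1: the ICC at fixed error.** ICC = B² / (B² + E²), with B the between-patient SD and E the error SD. Set E = 10 (assumed).

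- B = 10: 100/200 = 0.50
- B = 15: 225/325 = 0.69
- B = 20: 400/500 = 0.80
- B = 30: 900/1,000 = 0.90

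The same error fails or passes 0.7 according to spread alone.

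**Step 2: mixing in no-need patients.** Assume a 0–100 score. Patients with needs have mean 50, SD 20 (variance 400) and within-group ICC *r*. A share *p* sits at 100 on both measures. The variance between the two groups is p(1−p) × 50², so

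pooled ICC = [(1−p) × 400r + p(1−p) × 2,500] / [(1−p) × 400 + p(1−p) × 2,500].

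For p = 0.2 and r = 0.5: (160 + 400)/(320 + 400) = 560/720 = 0.78.

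| ICC among patients with needs | p = 20% | p = 30% | p = 50% |
|---|---|---|---|
| 0.30 | 0.69 | 0.76 | 0.83 |
| 0.50 | 0.78 | 0.83 | 0.88 |
| 0.60 | 0.82 | 0.86 | 0.90 |

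In this model the disagreement among patients with needs is the same in every column. For r = 0.5 the SD of the differences is √(2 × 0.5 × 400) = 20, so the limits of agreement span ±1.96 × 20 = ±39 points while the pooled ICC reads 0.78 to 0.88.

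**Step 3: a short form built as the plan describes.** Simulation of 200,000 patients: a total of 10 three-level items scaled to 100, predicted by least squares from the kept items, with no-need patients at the top on all items. Here 2 items are kept and the latent item correlation among patients with needs is 0.1–0.2.

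| No-need share | Pooled ICC | ICC, patients with needs | Mean absolute error, patients with needs |
|---|---|---|---|
| 0% | 0.48–0.59 | 0.48–0.59 | 11–12.5 points |
| 20% | 0.72–0.76 | 0.52–0.64 (20% and 40%) | 13–14 points |
| 40% | 0.81–0.83 | as above | about 15 points |

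The criterion improves while the error worsens, because the ceiling patients also pull the fitted equation.

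**Step 4: does the categorical analysis catch it?** With illustrative cut-offs at 50 and 90:

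- 2 items kept, 20–40% no-need: overall three-level kappa is 0.24–0.65. This form fails the plan's kappa limit.
- 4 items kept, 40% no-need: overall kappa is 0.78–0.79. The two need categories give 0.65–0.70, so category-specific output would show the weakness.
- 5 items kept, correlation 0.2, 40% no-need: every category is at or above 0.74, yet kappa among patients with needs is 0.64. Nothing in the planned output shows this, because one-category-versus-rest kappa still counts no-need patients in the rest.

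**Step 5: kappa does not always rise.** On a two-level scale with sensitivity 0.8 and specificity 0.95, kappa is 0.75 when 50% have the need. At 5%, observed agreement is 0.04 + 0.9025 = 0.9425, chance agreement is 0.05 × 0.0875 + 0.95 × 0.9125 = 0.8713, and kappa = 0.0712/0.1287 = 0.55. With sensitivity 0.6 and specificity 1.0 it goes the other way, from 0.60 to 0.74.

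**The case against.** A reader might infer that ICC, tau-b and kappa are all judged once on the pooled sample and that all three are inflated. The text does not support that. Tau-b and kappa are examined overall and by category, which is a breakdown by level of need, and step 5 shows that kappa can fall when need is rare. A reader might also infer that a poor short form will pass the plan as a whole. In step 4 the 2-item form that passes the ICC fails kappa, so the criteria work partly as complements.

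The inputs are also open to challenge. The document gives no no-need share, item correlation or number of kept items. Latent correlations of 0.1–0.2 imply a 10-item alpha of only 0.46–0.65 among patients with needs. At 0.4 or more, the ICC among patients with needs is at least 0.74 even with 2 items kept.

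Finally, all adults in these units are the intended users, so a pooled ICC is a valid quantity for them. Agreement by age or clinical profile is detail an article may leave to the analysis plan, and its absence is no finding.

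All of this stands, and it narrows the point without removing it. The ICC is the only criterion on the score itself, and its limit is fixed in the text. The category-specific output does not touch it, and the text does not say that every category must exceed 0.7. On a two-level instrument, category kappa equals overall kappa, and tau-b has no clear category-specific form. Cross-validation keeps the same case mix in its folds unless they are stratified.

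**Conclusion.** The point holds for the score-level criterion. A single pooled ICC > 0.7 does not show how well the short form measures patients with needs, and the planned categorical analysis fills that gap only in part.

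The size depends on two unknowns. At latent correlation 0.1–0.2 with 20% or more of patients at the no-need end, a form with an ICC of 0.52–0.64 among patients with needs passes at 0.72–0.83, with a mean absolute error of 13–15 points on 100. At correlation 0.4 or more the ICC failure disappears. The document settles neither unknown, so the result is a weakness in the criterion and not evidence that VALENF-HAD will perform badly.

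**What to change.** Keep the pooled ICC and add the following to the third phase:

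- For each original instrument, cross-validated mean absolute error, mean difference and limits of agreement in score points, overall and by need level. Need level can be the instrument's own categorical levels or, at the least, the sample without patients at the no-need extreme.
- Kappa among patients with needs, beside the overall and category-specific values.
- A statement of whether 0.7 applies to each category or only overall.
- A claim of equivalence limited to the levels where the error is acceptable, with acceptable error stated in score points before analysis starts (planned for 01/09/2026).

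Do not make ICC > 0.7 a pass rule within age or clinical-profile strata. Range restriction lowers the ICC there, and those strata do not separate patients with needs from those without. Error in points is not wholly free of case mix either, as step 3 shows, but it can be read directly at each level.

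The cost is wording and a little more output from data already being collected, with wider intervals per level.
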